### Dissemination

Results of this research will be presented at national and international conferences on topic and published in a peer-reviewed journal.

### Data monitoring and management

A data monitoring committee has not been necessary because the study is considered to be of minimal risk. The paper and pencil tests and questionnaire will be stored in a locked cabinet and will be entered in an electronic file. The access to these data will be permitted to the research members only. Any adverse events will be reported by filling in the appropriate form. The data that support the findings of this study will be openly available on Zenodo.

## Discussion

With this trial we present a novel clinical intervention combining music exposure with NIBS in DOC patients, also assessing the impact of this rehabilitation protocol on caregiver’s burden and psychological distress. Both music and NIBS have been largely proven effective in the realm of brain lesions. Nonetheless, this is the first study to propose a clinical protocol including a combined effect of these two intervention strategies among post-coma patients. Further strengths of the current protocol are the sample size and the use of a variety of objective measures, including neurophysiological ones such as EEG, to show the cognitive and functional improvement of DOC patients.

In relation to EEG recorded during music stimulation, our intervention is expected to produce two outcomes. The first consists of increased evoked responses amplitudes to sounds reflecting a residual plasticity of the auditory cortex in DOC patients after the music-based intervention combined with electric stimulation. Second, the continuous EEG is expected to display a decrease of power spectra of slow frequency bands and an increase in power for faster frequency bands. Overall, our ambitious aim of inducing and evaluating beneficial effects of music and brain stimulation on psychological and neurophysiological measures would represent a novel rehabilitation approach, not yet explored in DOC patients.

The experimental paradigm we designed is one of the major strengths of the study. Indeed, as RCTs provide the most reliable evidence on the effectiveness of interventions, a pivotal condition especially in clinical research, this protocol significantly contributes to shed light on the most appropriate characteristics for DOC-targeted interventions. As such, this study may help pave the way towards a more generalised and replicable protocol on DOC rehabilitation, as well as highlight the potential role of music on brain injury rehabilitation. In this sense, as our experimental design includes both preferred and non-preferred musical stimuli, this study will allow us to entangle the beneficial effects of music ascribable to its acoustic characteristics from those arising from its autobiographical content, yet unexplored in prior studies on DOC [27, 46]. A deeper understanding of musically-induced positive emotions in DOC patients might be central in sharpening cognitive stimulation processes and personal memory activation. This is particularly relevant for the clinical population we are considering as DOC can be related to damage of the dopaminergic system [26]. In other words, as rewarding music can activate the dopaminergic system via changes in the limbic system (i.e., [73]), the association between music stimulation and cognitive improvements in DOC might be mediated by musically-related positive emotions.

Another strength of this trial refers to its implications on the caregiver. Taking care of patients with DOC has a high impact on a caregiver’s social, economic and emotional condition. High levels of depression, anxiety and prolonged grief were reported both at admission both at follow-up in caregivers of DOC patients [74]. However, most music interventions studies have focused on caregivers of patients affected by dementia (for a review see [75]). As far as we know, there are no studies assessing the effects of music stimulation on DOC patients’ caregivers’ burden. We aim to fill this gap considering that music may be an efficient additional caring tool for caregivers for several reasons. First, in our study caregivers actively contribute to the intervention by suggesting patients’ musical preferences to the neuropsychologist and the experimental team. This direct involvement is likely to promote caregivers’ empowerment and increased control, as seen in previous studies (i.e., [76, 77]). Second, music-based interventions are generally associated with fostered feelings of inner strength, personal growth, increased resilience, social confidence and self-esteem amongst caregivers [76]. Therefore, our rehabilitation protocol could be valid and effective in relieving caregiver’s emotional symptoms.

We also acknowledge some limitations that should be considered for the interpretation of the results. First, since our experimental paradigm provides for tailored salient emotional stimuli (namely preferred music), individual differences on music reward sensitivity might influence the elicited responses. Indeed, prior evidence suggested that individual music reward sensitivity affects both physiological (skin conductance) and neural (mainly dopaminergic mesolimbic reward system) responses (see [78, 79]). A second potential limitation is related to the possible overestimation of the treatment effect size, due to the lack of studies performing this multimodal intervention on DOC patients. Accordingly, in the event of preliminary analyses revealing an effect size significantly lower than predicted, we will consider an extension of the population size. Lastly, given the nature of our target population and intervention, which involves specialised healthcare professionals and specifical equipment, we are unable to blind participants and assessors. All in all, this protocol has a high clinical applicability, it is easy to offer, and it is very motivating for the patients and the caregivers. We, therefore, believe that our findings may help to open new paths in the development of new specific DOC rehabilitation approaches.

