### Sample size determination

The effect size to be expected is uncertain as no study so far has implemented a combined intervention of music and electrical stimulation in DOC patients. We assume it to be in the medium-to large range (i.e., Cohen’s d between 0.5 and 0.8). We aim to achieve 80% power (*f* = 0.30) in a repeated-measures analysis of variance (*a* = 0.05, power (1-b) = 0.80) with condition as between-subject factor (tES combined with music stimulation vs. sham stimulation, and noise vs. music stimulation and sham stimulation), and time (pre-intervention, post-intervention and post-placebo), as within-subject factor. Power calculations (using G* Power 3) indicate that a valid sample size of *n* = 10 per group will result in 80% statistical power if the effect is *d* = 0.68, which is in the medium-to-large range. This results in a total sample size of *n* = 30.

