### Data analysis

The SPSS 23.0 statistical software will be used for the data analysis. All the statistical hypotheses will be tested by two-side test, with statistically significant test level set at 0.05 and the confidence interval estimation to 95%.

The aim of our study is to evaluate the effects of the treatments in the various patient groups on the primary and secondary outcomes. Descriptive analysis of the data will allow us to identify the characteristics of the groups. Comparison of demographic and clinical characteristics of the groups will be performed using one-way ANOVA for continuous variables and the Chi-square test for categorical variables. Considering the crossover and longitudinal aspects, primary analyses will focus on behavioural changes at group level, comparing the treatments. Moreover, at the individual level, we will analyse the differences between pre-treatments and post treatments data.

As for the primary outcomes, we will measure the effects of the intervention on the following measures (two neurophysiological and two clinical and behavioral): (i) power spectra of frequency band extracted from the EEG recordings; (ii) auditory evoked responses, extracted from the EEG recordings; (iii) behavioural responses of DOC patients, measured through CRS-R.

Baseline characteristics and carryover effect will be analysed between the three sequences using ANOVA and chi-square test. By including the order of intervention as a covariate, we aim to determine whether the sequence in which participants receive the interventions impacts the observed outcomes. To assess the presence and magnitude of the washout effect, we plan to incorporate appropriate statistical methods into our analysis, such as comparing outcomes during the washout period to those observed during active treatment phases. To this end, we will use repeated measures ANOVA considering time (before, during, and after the washout) as the independent variable, with behavioral measurements as the dependent variables.

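### The sample may be extended after a look at the treatment effect, with all tests at 0.05 and no alpha reserved, so the 5% error rate is not guaranteed

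*Protocol article*

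**What the plan says.** Four places in the protocol article bear on this.

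- **Discussion, limitations paragraph.** The authors concede that they may have overestimated the effect size, and continue: "in the event of preliminary analyses revealing an effect size significantly lower than predicted, we will consider an extension of the population size".
- **Data analysis.** The sidedness is fixed for every hypothesis: "All the statistical hypotheses will be tested by two-side test". The same sentence fixes the level: "with statistically significant test level set at 0.05". No other level is given for a test that follows a look or an extension.
- **Sample size determination.** The target is stated as follows: "We aim to achieve 80% power (*f* = 0.30) in a repeated-measures analysis of variance". Of the chosen ten patients in each arm, the article says that this number "will result in 80% statistical power if the effect is *d* = 0.68, which is in the medium-to-large range". Three arms make 30 patients. The calculation uses the full 0.05 for a single analysis at that size.
- **Data monitoring and management.** "A data monitoring committee has not been necessary". The article does not say who would run the preliminary analyses.

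**The concern.** An effect size for a treatment comparison cannot be computed without condition labels, so the look differs from a blinded check of variability. A good first result stands at 30 patients, while a poor one brings more patients and a test of the enlarged sample. If that test also uses 0.05, a null treatment can get a second chance at significance, and the overall error can exceed 5%. The final effect estimate would also depend on what the look showed.

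The clause could well be used. The article calls the expected effect uncertain and possibly overestimated, and an estimate from 10 patients per group is noisy.

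This is more than a detail that an article leaves out. It states an effect-driven extension and a fixed 0.05 level, and nothing in it reconciles the two.

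**Working it through.** **The plan's own figure.** The inputs are N = 30, three groups, three times, alpha 0.05, power 0.80, and f = 0.30 alongside d = 0.68 (f = d/2 = 0.34). The article does not state the within-patient correlation ρ or which effect is tested, so N = 30 does not follow from a single calculation.

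- Group-by-time interaction, λ = f²·N·3/(1−ρ), with 4 and 54 degrees of freedom. At f = 0.30 and ρ = 0.5, λ = 0.09·90/0.5 = 16.2 and power is 0.887. Power is 0.80 at ρ of about 0.38.
- Within-patient effect at f = 0.34 and ρ = 0, with 2 and 54 degrees of freedom. λ = 0.1156·90 = 10.4 and power is 0.809.
- Plain two-sample t-test, 10 per group, d = 0.68: power is 0.30.

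The point below does not depend on which of these was meant. None of them sets alpha aside for a look.

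**Type I error if the clause is used.** From the article: 10 per group, predicted d = 0.68, two-sided 0.05. Assumed, because the article is silent: a look at 10 per group; extension to 15, 20 or 30 per group; one outcome; a two-group t-test on the pooled data at 0.05. Trials were simulated with no true effect. If the observed signed d is below the threshold, the trial is extended and tested at the larger size. Otherwise the test at 10 per group is final.

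The word *significantly* in the trigger can be read loosely or statistically, so three thresholds were used. For the statistical reading, the standard error of d at 10 per group is about √(2/10) = 0.447, and 0.68 − 1.96·0.447 = −0.20.

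| Extend if signed d is below | Overall error at 15 / 20 / 30 per group | Benefit-side error (nominal 0.025) |
|---|---|---|
| 0.68 | 0.056 / 0.060 / 0.064 | 0.031 / 0.035 / 0.039 |
| 0.3 | 0.050 / 0.052 / 0.055 | 0.025 / 0.027 / 0.030 |
| −0.20 | 0.050 / 0.049 / 0.047 | about 0.025 throughout |

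With the 0.68 threshold, about 93% of null trials are extended.

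**Closer to the planned model.** A three-group, three-time interaction F-test was simulated with a look at 5 or 10 per group, extension to 15–30 per group, and a trigger of observed f below 0.30 or 0.20 (scaled with ρ = 0.5). The overall error was 0.052 to 0.081. An F-test has no direction, so this rule cannot represent a signed shortfall.

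**Level that restores 5%.** If the data are tested at 30 patients and again after an extension, the unadjusted overall error is about 0.077, 0.083 or 0.088 for extension to 1.5, 2 or 3 times the size. A common nominal two-sided level of about 0.032, 0.029 or 0.028 brings it back to 0.05.

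**The case against.** The strongest reply is that the text does not establish inflation. The trigger is directional and asks for an effect significantly below prediction. Read statistically, that extends only when the observed d is under about −0.2, and the error then stays at or just below 5%. This stands, and the size must be stated as conditional on the trigger.

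A second reply is that the article says only that an extension would be considered, in a limitations paragraph. Protocol changes go to the ethics committee, and an analysis plan that is not shown could hold an adjustment. This stands in part: the 0.05 level after an extension is the only one given, not one confirmed for that case. But ethics approval does not control type I error, and a discretionary rule has no calculable error rate.

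Two stronger readings are tempting and are not supported.

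- A reader might infer that the trial is extended whenever the first result is not significant, which gives 7.8–8.9% under the same assumptions. The document's trigger is an effect size, not a p-value. A rule on the absolute value, |d| below 0.68, gives about 6.1–7.9%, but it ignores the direction in the text.
- A reader might infer that the investigators would see the interim effect because there is no monitoring committee. The article explains the missing committee by minimal risk and does not say who would see the look. It also places randomisation with an independent researcher.

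**Conclusion.** The point holds in a limited form. The article allows an extension driven by the estimated treatment effect, sets all tests at 0.05 and reserves no alpha, so the 5% rate is not protected if the clause is used.

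The size is not determined by the document. For a directional trigger and a two-group t-test it runs from essentially no inflation to about 1.4 percentage points overall (6.4% against 5%). On the benefit side the largest figure is likewise 1.4 points (3.9% against 2.5%). These figures are per outcome and rest on the assumed look, thresholds and extension sizes. They do not show that the trial's error rate will be inflated, only that nothing in the article prevents it. The clause should be changed before anyone sees comparative data, because a clean repair afterwards is not possible.

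**What to change.** Replace the sentence in the limitations paragraph by one of two rules, and repeat the rule under Sample size determination.

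- **(a) Blinded revision.** The sample size may be revised once, using only the pooled SD and the within-patient correlation computed without condition labels. The final test stays at 0.05, and the error rate is kept at least approximately.
- **(b) Planned look at the effect.** Name one look, its timing, the maximum sample size, and a combination test with fixed weights or an adjusted level. For two equal looks (30 patients, then 60) the level is about 0.029 at each.

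Either takes one paragraph and leaves treatment unchanged. Option (a) is the simpler and costs no alpha, but it gives up reacting to a small effect. Option (b) keeps that possibility and slightly lowers the nominal level.
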